### SAIA-Naloxone specialist activities

Our study team will hire and train specialists with experience distributing naloxone in SSPs and who are familiar with SSP culture. The specialist training will leverage mock data to simulate the steps of SAIA-Naloxone and focus on electronic data collection instruments, the NCAT, racial disparities, anti-Black racism, and racial equity tools for overdose prevention. After training, the study team will provide weekly supervision to specialists throughout the 12-month active phase, with more intensive supervision during the first 2 months.

For SSPs in the experimental arm, specialists will partner with site leadership and frontline staff during the 12-month active phase. The specialist will meet with these individuals twice per month for the first 3 months and once per month for the remaining 9 months. Specialists will be allotted 45 h of time to deliver SAIA-Naloxone to each SSP (3 h per meeting: 1 h for the meeting itself and 2 additional hours for time spent preparing for or following up after the meeting), which aligns with the amount of time allotted for similar activities in the original SAIA trial [19]. At the first visit, the specialist will discuss the naloxone delivery cascade and SAIA-Naloxone in detail with SSP staff, observe the SSP’s process for distributing naloxone, and review data collection approaches. Having laid this groundwork, the specialist will guide the SSP through the three iterative steps of SAIA-Naloxone until achieving desired change.

### Trial variables and data collection

#### Implementation determinants and context variables

Our naloxone pilot study identified implementation climate and leadership engagement as important implementation determinants that can be influenced by SAIA-Naloxone and ultimately improve naloxone distribution among SSPs [28]. Therefore, in the present study, we will assess change in implementation climate and leadership engagement over time. We will first collect SSP-specific contextual data at randomization (baseline) and 12 months after randomization from all enrolled sites. We will ask the primary contact at each SSP about basic organizational characteristics (location, number of staff, budget, etc.). Next, we will ask the primary contacts as well as other staff involved with naloxone distribution at each SSP about contextual variables such as implementation climate and leadership engagement for improving naloxone distribution [41–43].

#### Fidelity variables

We will assess SAIA-Naloxone fidelity at the specialist level. Assessment will utilize descriptive statistics such as means/medians, standard deviations/interquartile ranges, and ranges given the small sample of specialists employed by the study (*n* = 2). Fidelity to SAIA-Naloxone focuses on assessing the domains of content, coverage, frequency, duration, quality, and participant responsiveness of SAIA-Naloxone. To monitor fidelity, all meetings between SAIA-Naloxone specialists and SSPs will be audio recorded, and the specialist will document each meeting with an SSP in a site-specific encounter log that includes the duration of the encounter, the roles of meeting attendees, and which of the three steps the specialist completed. Study staff will rate meeting content, quality, and participant responsiveness by reviewing 20% of recorded sessions using a fidelity checklist. To assess frequency, duration, and coverage, study staff will review and assess each encounter log.

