Actions		1. Identify gaps: a. Present data evaluating the SSP’s naloxone delivery cascade with NCAT b. Facilitate discussions and support the implementation team to identify and develop consensus with regards to the areas of attrition along the naloxone cascade that they would like to address 2. Identify causes and opportunities: a. Facilitate discussions with the implementation team to review the SSP’s service structure and draw process maps documenting the flow of participants through the naloxone delivery cascade to understand (i) why there are drop-offs or inequities in distribution at different points (root causes of participant attrition) and (ii) what it would take to address those issues (opportunities to streamline workflows and address key points of attrition) b. Assist team in developing consensus about programmatic modifications based on their importance and feasibility 3. Conduct CQI: a. Support and mentor the implementation team in operationalizing programmatic modifications b. Present follow-up data on the naloxone delivery cascade for the implementation team to assess changes resulting from programmatic modifications c. Repeat above actions after conclusion of the cycle
Action target		Leverage programmatic data to facilitate CQI and foster a learning climate
Temporality		After training the implementation team on the SAIA process and integrating enhanced instruments to collect program data into workflows to track naloxone delivery cascade indicators
Fidelity		Content: Specialist completes actions 1–3 with SSPs Coverage: Relevant SSP staff are present during actions 1–3 Duration: Actions 1, 2, and 3 take ~ 60min each Frequency: Specialist visits SSPs in person during months 1, 4, 7, and 10. Specialist meets SSPs virtually during all other months in active phase Quality: Specialist forms rapport with SSP staff, flexibly attends to their unique needs, and motivates SSP staff to engaged with actions 1–3 Participant responsiveness: SSP staff like working with the specialist and like participating in actions 1–3

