To evaluate these aims, we plan a randomized controlled interrupted time series trial with 32 SSPs in California. We will randomly assign 16 SSPs to the SAIA-Naloxone arm and 16 SSPs to IAU (Fig. 1). SSPs randomized to the IAU arm will not receive support to improve naloxone distribution. SSPs in California have already adopted naloxone distribution. We are therefore testing the ability of SAIA-Naloxone to optimize naloxone distribution within SSPs. Accordingly, we characterize IAU by the absence of SAIA-Naloxone with the goal of comparing whether SAIA-Naloxone improves SSPs’ Naloxone distribution. We will harmonize primary outcome data collection across SSPs receiving SAIA-Naloxone and IAU as described in the “Trial variables and data collection” section below.

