#### Primary outcome variables

Primary outcomes center on the multidimensional variable of implementation effectiveness. Implementation effectiveness “is an organization-level construct that refers to the aggregated consistency, quality, and appropriateness of innovation use within an organization” [44]. Implementation effectiveness fits our broad objectives, focused on the extent to which SAIA-Naloxone impacts naloxone distribution at the organizational level. Accordingly, SSPs represent the primary unit of analysis. The Proctor et al. (2011) taxonomy of implementation outcomes forms our operationalization of implementation effectiveness, focusing on SSPs’ reach of naloxone screening and fidelity to naloxone cascade completion [45].

Aim 1 focuses on SAIA Naloxone’s ability to improve implementation effectiveness relative to IAU. We will assess “reach” as a proxy for the implementation effectiveness concepts of appropriateness and consistency, evaluating the number of participants screened for naloxone engagement, while accounting for the total number of participants who present for services. We will assess fidelity (i.e., fidelity to cascade completion) as a proxy for the implementation effectiveness concept of quality, evaluating the number of people who receive naloxone, again accounting for the total number of SSP participants screened for naloxone distribution. We collected similar indicators from SSPs in prior studies due to their utility in analyses and feasibility during collection [9, 10, 28]. Aim 2 focuses on SAIA-Naloxone’s ability to improve implementation effectiveness for BIPOC and other key participant subgroups relative to improvements in SSP participants overall. Therefore, operationalization of Aim 2 outcomes mirror those from Aim 1 but with a focus on those groups. Furthermore, our focus on the overall and disaggregated proportion of people receiving naloxone stems from a strong body of research showing that such outcomes significantly predict opioid overdose mortality rates at the SSP level [46–48].

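### Fidelity is to be assessed by specialist (n = 2), which can mask poorly served SSPs; a summary by SSP (n = 16) from the same records would serve the type III judgement better

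*Protocol article*

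**What the plan says.** Under Fidelity variables, the protocol article fixes the unit of assessment: "We will assess SAIA-Naloxone fidelity at the specialist level". The method follows: "Assessment will utilize descriptive statistics such as means/medians, standard deviations/interquartile ranges, and ranges". The reason offered is "given the small sample of specialists employed by the study", with n = 2 in brackets.

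The same section describes the records. All meetings are audio recorded. Each meeting is entered in a log kept separately for each site, with its length, the roles of those attending and the SAIA step completed. Study staff review every log for frequency, duration and coverage. Content, quality and participant responsiveness are rated by "reviewing 20% of recorded sessions using a fidelity checklist".

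Elsewhere the SSP is the unit. Under Trial aims and hypotheses: "We will randomly assign 16 SSPs to the SAIA-Naloxone arm and 16 SSPs to IAU". Under Primary outcome variables: "Accordingly, SSPs represent the primary unit of analysis". In Table 1, coverage depends on whether the right SSP staff attend, responsiveness on how SSP staff take to the specialist and the activities, and frequency on contact with each SSP.

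Specification and fidelity assessment, and again the Discussion, give fidelity a purpose: to help judge a type III error, that is, whether a null result comes from poor delivery and not from the strategy.

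**The concern.** Fidelity is wanted here to separate a strategy that failed from a strategy that was not delivered. Delivery happens, or fails to happen, at the SSP. If a minority of SSPs engage poorly, the shortfall appears as variation between sites. A summary organised around two specialists pools that variation away, particularly if each specialist has a similar share of weak sites. The reader of a null or diluted result would then see two similar, fairly high figures and could conclude that delivery was adequate.

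The choice is explicit, so this is not a matter of detail left to a fuller document. The n = 2 given as the reason for a descriptive approach suggests that the specialists are being counted as the units, although 16 site-level units are available at no extra cost.

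**Working it through.** **1. The plan's own figure.** Under SAIA-Naloxone specialist activities, meetings take place "twice per month for the first 3 months and once per month for the remaining 9 months", at 3 h of specialist time each.

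- Meetings per SSP: 2 × 3 + 1 × 9 = 15.
- Hours per SSP: 15 × 3 = 45 h, which matches the stated 45 h.
- All meetings in the arm: 16 × 15 = 240, or 120 per specialist if the SSPs are split evenly. The even split is an assumption, as the article does not state the allocation.

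**2. Masking under a specialist-level mean.** Assume eight SSPs per specialist, with k of the eight receiving 5 of 15 meetings and the rest all 15. The specialist mean is (5k + 15(8 − k))/8. The figures 5 and k are illustrative; k is varied to show the range.

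| k per specialist | Weak SSPs of 16 | Each specialist's mean | Between-specialist SD | SSP range | SSP SD |
|---|---|---|---|---|---|
| 1 | 2 | 13.75/15 = 92% | 0 | 5–15 | 3.4 |
| 2 | 4 | 12.5/15 = 83% | 0 | 5–15 | 4.5 |
| 3 | 6 | 11.25/15 = 75% | 0 | 5–15 | 5.0 |

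For k = 2, the SSP-level SD comes from four deviations of −7.5 and twelve of +2.5: (4 × 56.25 + 12 × 6.25)/15 = 20, and √20 = 4.5.

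The equal spread of weak sites is the case most favourable to masking. If all four weak SSPs belonged to one specialist, the means would be (4 × 5 + 4 × 15)/8 = 10, or 67%, against 100%. A problem would then be visible, but it would appear as a difference between specialists and would still not show which sites were affected.

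**3. The rated recordings.** If all meetings are held, 20% of 240 is 48 recordings, an average of 48/16 = 3 per SSP and 24 per specialist. The article does not say how the 20% is drawn. Two cases bound the matter:

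- Spread evenly over SSPs: every SSP has 3 of 15 rated, and none is missed.
- Simple random draw of 48 from 240 (assumed): the hypergeometric chance that a given SSP has none is 0.031, so 16 × 0.031 = 0.50 SSPs are expected to have none. The simulated chance that at least one SSP has none is about 42%. About 16 × 0.158 = 2.5 SSPs are expected to have at most one.

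This bears only on content, quality and responsiveness. Frequency, duration and coverage use all logs.

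**4. Frequency standard.** Table 1 has: "Specialist visits SSPs in person during months 1, 4, 7, and 10", with virtual contact in the other active months. That gives the mode of contact by month. The text gives the count, 15. A schedule of 15 meetings satisfies both.

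**The case against.** The strongest reply is that the section supplies what is needed to see poor delivery. Logs are kept by site and every one is reviewed, so weak SSPs can be identified for frequency, duration and coverage. This stands. A reader might infer that the plan cannot show where SAIA-Naloxone was poorly delivered; the documents do not support that.

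Second, working at the specialist level need not mean one number per specialist. It may mean whose delivery is being judged, which would separate this fidelity from the SSP's fidelity to the naloxone cascade, a second use of the word in the article. Medians, IQRs and ranges also make more sense over each specialist's meetings than over two values. This stands as a possible reading. It follows that the imprecision of an SD from two values (95% limits 0.45 to 31.9 times the estimate, against 0.74 to 1.55 times with 16) should carry no weight: it assumes one value per specialist and an inference to other specialists that the plan does not make. Even on this reading the masking is only partly relieved. A spread over meetings held can reveal short or poorly attended ones, but a count of missed meetings needs an expected number for each SSP.

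Third, the way the 20% is drawn is detail that an article may leave to the full protocol. That is fair, and the 42% is conditional on a draw that the article does not state. It illustrates why spreading the sample is worthwhile and does not show a fault in the plan.

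Fourth, a reader might infer that Table 1 and the meeting schedule contradict each other, giving frequency two denominators. They do not: one states mode, the other count.

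Finally, the type III judgement can be made for the trial as a whole from pooled logs, and no aim or hypothesis depends on fidelity by SSP. Both are true, and they limit the point to a descriptive measure that aids interpretation.

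**Conclusion.** The point holds in a limited form. The article names the specialist, n = 2, as the unit for fidelity, while delivery, several of the fidelity domains and the outcome analysis all sit at the SSP. A summary on that unit can hide poorly served sites: in the illustration, four of 16 SSPs receive a third of their meetings, yet both specialist means are 83% with no difference between them. That rests on an even split of SSPs, an equal spread of weak sites and the assumed 5 of 15 meetings; across the cases shown, the specialist means run from 75% to 92% while the SSP range stays at 5–15.

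The effect is to weaken the type III judgement, not to rule it out. The data are planned and sufficient for the three domains taken from the logs; for the three rated domains, sufficiency at every site depends on how the recordings are chosen. The primary analysis, alpha and power are unaffected.

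**What to change.** - State that all fidelity domains will be summarised by SSP (n = 16), using the planned site logs and ratings, with the specialist shown as a descriptor.
- State that the 20% of recordings will be spread over SSPs, about 3 of 15 each, so that content, quality and responsiveness are observed at every site.
- Optionally, add to Table 1 the count of 15 meetings per SSP, so that frequency has an explicit expected number beside the mode of contact. The two sections are compatible as written, so this is a clarification only.

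The cost is a change of wording. The logs stay the same, and the number of recordings rated stays at about 48.

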#### Primary outcome variables

Primary outcomes center on the multidimensional variable of implementation effectiveness. Implementation effectiveness “is an organization-level construct that refers to the aggregated consistency, quality, and appropriateness of innovation use within an organization” [44]. Implementation effectiveness fits our broad objectives, focused on the extent to which SAIA-Naloxone impacts naloxone distribution at the organizational level. Accordingly, SSPs represent the primary unit of analysis. The Proctor et al. (2011) taxonomy of implementation outcomes forms our operationalization of implementation effectiveness, focusing on SSPs’ reach of naloxone screening and fidelity to naloxone cascade completion [45].

Aim 1 focuses on SAIA Naloxone’s ability to improve implementation effectiveness relative to IAU. We will assess “reach” as a proxy for the implementation effectiveness concepts of appropriateness and consistency, evaluating the number of participants screened for naloxone engagement, while accounting for the total number of participants who present for services. We will assess fidelity (i.e., fidelity to cascade completion) as a proxy for the implementation effectiveness concept of quality, evaluating the number of people who receive naloxone, again accounting for the total number of SSP participants screened for naloxone distribution. We collected similar indicators from SSPs in prior studies due to their utility in analyses and feasibility during collection [9, 10, 28]. Aim 2 focuses on SAIA-Naloxone’s ability to improve implementation effectiveness for BIPOC and other key participant subgroups relative to improvements in SSP participants overall. Therefore, operationalization of Aim 2 outcomes mirror those from Aim 1 but with a focus on those groups. Furthermore, our focus on the overall and disaggregated proportion of people receiving naloxone stems from a strong body of research showing that such outcomes significantly predict opioid overdose mortality rates at the SSP level [46–48].

We will harmonize primary outcome variable collection timing between SAIA-Naloxone and IAU SSPs, with both submitting data electronically on a fixed schedule. SSPs will receive prorated financial incentives for the number of completed data submissions at 6, 12, and 18 months after randomization. Based on our prior work, we anticipate retaining 98% of SSPs’ data submissions for 12 months after randomization and 92% of submissions at 18 months [28].

#### Cost and cost-effectiveness variables

We will collect cost outcomes using a modified version of the Substance Abuse Services Cost Analysis Program (SASCAP) [49], widely applied and adapted to a variety of behavioral and public health interventions [50–55]. The modified SASCAP will capture resource use and costs from the SSP provider perspective, as this perspective best aligns with SAIA-Naloxone’s focus on improving the naloxone delivery cascade as measured by the number of people receiving naloxone (including disaggregated numbers for BIPOC and other key subgroups) and the number of doses distributed. To collect the resources used for each of the three SAIA-Naloxone steps, the SASCAP will systematically track the time, space resources, and any material resources utilized by SAIA-Naloxone specialists and SSP staff involved in the strategy over the active and sustainment phases. We will also collect data on the time spent training SAIA-Naloxone specialists, SSP staff wages, building costs, and material costs.

### Data analysis and power calculation

Before model fitting, we will assess whether there is significant variation across the three potential levels of aggregation for each outcome: (1) within-SSP level (repeated measures over time), (2) between-SSP level, and (3) county level. We will also examine the functional form of changes over time in outcomes. We assume that piecewise linear (i.e., linear change during the 3-month lead-in period, post-implementation linear change from baseline through 18 months, and a period of treatment effect “deterioration” (if any) between 12 and 18 months) will be the predominant functional form, though with this large number of assessments, nonlinear forms may be necessary [56–58]. We will estimate a random intercept (*π*_*0is*_), which is the estimated (conditional) mean value of the outcome at time = 0 (e.g., lead-in baseline), and two random slopes (*π*_*1is,*_* π*_*2is*_): (1) the estimated per-year change in Y from the lead-in phase through 18 months; and (2) the “deterioration” phase, capturing how much reduction there is in change over the last year, if any, for the SAIA-Naloxone condition.

Level 2 will examine the between-SSP level effects. The key predictor included in *X*_*qis*_ is a 0/1 dummy indicator indicating whether SSP *i* was in the SAIA-Naloxone condition or IAU. *β*_*1s*_ will capture the average change over time in naloxone distribution (and other outcomes), which (1) should not be significantly different from zero during the lead-in period and (2) will vary by SAIA-Naloxone and IAU after implementation (by virtue of the SAIA-Naloxone × time period 1 interaction). *β*_*0s*_ will capture the conditional mean level of naloxone distribution, which, if it varies by implementation condition, would capture a mean shift in our study outcomes. *β*_*2s*_ will capture the change over time in naloxone distribution during the second year; if it interacts with the SAIA-Naloxone indicator, it will capture slope differences over time beyond 1 year between SAIA-Naloxone and the IAU condition, with Year 1 gains maintained if this parameter estimate is nonsignificant.

Level 3 will capture county-level variability in intercepts and, if necessary, slopes over time. As mentioned previously, our Aim 2 analysis will use the subset of SSPs that report outcome data disaggregated by race, ethnicity, and gender. For both Aims 1 and 2, we will reject the null hypothesis (i.e., there are no differences between SAIA-Naloxone and IAU SSPs regarding the test statistics described above) if *p*-values are equal to or less than an alpha coefficient of 0.05.

We structured a Monte Carlo power analysis [59] using the parameters from our pilot. For Aim 1, we structured a population model based on the number of weekly data submissions from SSPs) with a binary predictor structured to have the following effects, using the lead-in period standard deviation across 1 year in the pilot (15.09) as the denominator for the effect size. The mean shift in post-implementation outcomes was 22.76 additional people served under SAIA-Naloxone, yielding a Cohen’s *d* of 1.50. The per-week increase in number served under SAIA-Naloxone was 1.29, reaching a longitudinal Cohen’s *d* effect size [60, 61] of 1.0 by 11 weeks. We generated 250 synthetic samples of *N* = 32 and analyzed the samples in Mplus while imposing the random effect structure from pilot estimates and a county-level intraclass correlation of 0.05. Specific to Aims 1 hypotheses that pertain to the active 12-month phase, we will have at least 80% power to detect a post-implementation mean shift and differences in slopes over time. Specific to Aims 1 hypothesis that pertain to the sustainment phase, detecting treatment effect deterioration from 12 to 18 months for 80% power requires deterioration equivalent to a Cohen’s *d* of 0.48. The extremely large number of repeated measures offsets the sample size of 32 with regard to statistical power to detect slope differences [62].

We will calculate cost estimates for each of the three SAIA-Naloxone steps. We will multiply the quantity of a resource (e.g., labor) used by its price (e.g., wage) and then calculate the average cost for each step. Our cost-effectiveness analysis approach will follow the methods our authorship group have implemented in previous studies [50, 51, 53–55]. We will combine our cost estimates with the estimated changes in outcomes, the number of people receiving naloxone, and the number of BIPOC receiving naloxone. To derive cost-effectiveness ratios, we will calculate the difference in costs and outcomes between the two arms. We will then calculate the incremental cost-effectiveness ratio (ICER) as the ratio of the difference in costs to the difference in outcomes. For example, for effectiveness defined as the number of people receiving naloxone, the ICER represents the incremental cost spent for an additional person receiving naloxone. We will also calculate cost-effectiveness acceptability curves (CEACs) [63–65]. The CEACs incorporate the inherent joint variability of the cost and effectiveness estimates, and they show the probability that an intervention is cost-effective as a function of the policymaker’s intrinsic valuation or willingness to pay for the clinical outcome. We will use nonparametric bootstrap methods to calculate CEACs.

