**Methods:**

We will conduct a trial with 32 SSPs across California, randomly assigning 16 to the SAIA-Naloxone arm and 16 to receive implementation as usual. SAIA-Naloxone is a multifaceted, multilevel implementation strategy through which trained facilitators work closely with SSPs to (1) assess organization-level barriers, (2) prioritize barriers for improvement, and (3) test solutions through iterative change cycles until achieving and sustaining improvements. SSPs receiving SAIA-Naloxone will work with a trained facilitator for a period of 12 months. We will test SAIA-Naloxone’s ability to improve SSPs’ naloxone distribution using an interrupted time series approach. Data collection will take place during a 3-month lead-in period, the 12-month active period, and for an additional 6 months afterward to determine whether impacts are sustained. We will use a structured approach to specify SAIA-Naloxone to ensure strategy activities are clearly defined and to assess SAIA-Naloxone fidelity to aid in interpreting study results. We will also assess the costs associated with SAIA-Naloxone and its cost-effectiveness.

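### The listed growth parameters contradict the plan's own three-segment form, and none of them is the post-implementation mean shift for which power is claimed

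*Protocol article*

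**What the plan says.** All of this is in the protocol article, under Data analysis and power calculation, unless noted.

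- **Functional form.** The plan expects a piecewise line: "linear change during the 3-month lead-in period, post-implementation linear change from baseline through 18 months", followed by possible deterioration between 12 and 18 months. Nonlinear forms are allowed if needed.
- **Parameters listed.** There is a random intercept, the "mean value of the outcome at time = 0 (e.g., lead-in baseline"), and two random slopes. The first is "the estimated per-year change in Y from the lead-in phase through 18 months". The second is the deterioration phase, placed in the last year, although the sentence before it says 12 to 18 months and the next paragraph speaks of the second year.
- **Interpretation.** The intercept coefficient, "if it varies by implementation condition, would capture a mean shift in our study outcomes". The first-slope coefficient is expected to be null in the lead-in and to vary by arm after implementation, through an arm by time-period-1 interaction. First-year gains count as maintained if the second-slope interaction is nonsignificant.
- **Power.** "The mean shift in post-implementation outcomes was 22.76 additional people served under SAIA-Naloxone", with 1.29 per week as the slope effect. The claim is that "we will have at least 80% power to detect a post-implementation mean shift and differences in slopes over time". Deterioration is detectable at 80% power from d = 0.48.
- **Timing** (section on randomization procedures, Table 2). The lead-in is months 1 to 3, randomisation is at month 3, the active phase is months 4 to 15 and sustainment is months 16 to 21.

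**The concern.** Three statements do not fit together: the assumed shape, the parameters listed and the effect powered.

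- **Shift.** If time 0 is the lead-in baseline, the arm difference in the intercept is a difference between sites not yet randomised. It measures chance imbalance and cannot be a shift that begins after implementation.
- **Slope.** A single line through the lead-in and the following 18 months has one gradient. It cannot be zero in the first part and arm-dependent in the second.
- **Level change.** The design is described as an interrupted time series, yet no listed term lets the level change at the interruption. Whatever the intercept and first slope cannot absorb passes into the deterioration slope.

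Aim 1's shift, slope and sustainment conclusions use these parameters. Aim 2 mirrors Aim 1, and the cost-effectiveness analysis uses the estimated changes in outcomes.

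**Working it through.** **Planning figures first.** 22.76 / 15.09 = 1.508 (stated 1.50). 1.29 × 11 / 15.09 = 0.94, and 15.09 / 1.29 = 11.7 weeks to reach d = 1.0 (stated 11 weeks). The Monte Carlo power cannot be reproduced because the pilot random-effect structure is not given. A rough two-mean calculation (16 per arm, difference 22.76, SD 15.09, two-sided 0.05) gives 98.9%. That is compatible with the stated figure of at least 80% but does not reproduce it.

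**Set-up.** The power section refers to weekly submissions. I took 3 + 12 + 6 months as 13 + 52 + 26 = 91 weekly points, t = 0 to 90, with treatment starting at t = 13 and the knot 12 months after randomisation at t = 65. The true arm difference is D(t) = a × [t ≥ 13] + b × max(t - 13, 0), with a = 22.76 and/or b = 1.29 from the protocol and no true deterioration.

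**Model as listed.** D(t) is projected by least squares on [1, t, max(t - 65, 0)]. No variances are involved. The deterioration d is slope 2 × 26 / 15.09.

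| True effect | Intercept contrast | Slope 1 per week | Slope 2 per week | Change over 26 weeks | d |
|---|---|---|---|---|---|
| Step 22.76 only | 8.4 | 0.29 | -0.559 | -14.5 | -0.96 |
| Step 22.76 plus 1.29/week | -2.4 | 1.46 | -0.316 | -8.2 | -0.54 |
| 1.29/week only | -10.8 | 1.17 | +0.244 | +6.3 | +0.42 |

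The correct deterioration value is 0 in every row. Small changes in where the week count starts move the middle row to about -2.9, 1.47 and d -0.57. Placing the knot 6 months after randomisation, as the last-year wording implies, gives slope 2 of -0.71, -0.41 and +0.30 per week.

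**Charitable reading 1: time 0 at randomisation.** This only re-centres the same fit. Step only: 8.415 + 13 × 0.291 = 12.2, about half of 22.76. Step plus slope: -2.385 + 13 × 1.458 = 16.6. Slope only: -10.8 + 13 × 1.167 = 4.4, where the truth is 0. Slope 2 does not change.

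**Charitable reading 2: the three stated segments, joined, without a step.** A purely gradual effect is now recovered exactly. A pure step gives an intercept contrast of -8.5, a spurious lead-in arm slope of 2.1 per week and deterioration of d = -0.31.

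**With a step and a slope change at randomisation.** The step-plus-slope pattern returns 22.76, 1.29 and 0 exactly.

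**Rejection rates (illustrative).** 1,500 simulated trials per setting, 16 against 16, using each site's least-squares coefficients and a t-test. Assumed, not in the document: residual and between-site SD 15.09, slope SD 0.1 or 0.3 per week, weekly autocorrelation 0 or 0.5. As listed, false deterioration was significant in 69–99% of trials for the step alone, 28–75% for step plus slope, and at most 0.3% for slope alone. With the added terms, the deterioration test rejected in 4–6%.

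**The case against.** The strongest defence is that the same section does describe a segment starting at baseline, and the context-variables section equates baseline with randomisation. The arm by time-period-1 interaction suggests period coding, lead-in baseline is offered only as an example of time 0, and nonlinear forms are left open. A condensed article need not print the coding of its time variables. A reader might therefore infer that nothing in the plan starts at randomisation; the document does not support so broad a statement. What stands is that the parameters it lists do not match the form it describes. Neither charitable reading supplies a level change, and an allowance for nonlinear forms does not say which parameter is tested.

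A reader might also infer that false deterioration always follows. It does not. It needs a step-like component, and the protocol's iterative improvement cycles, with time for startup, make an instant full jump the least typical shape. A gradual effect reverses the sign, and could then hide real deterioration.

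Nor does the coding manufacture efficacy. With no SAIA-Naloxone effect, every arm contrast still has expected value zero under randomisation. For a gradual effect, slope 1 is about 9% low (1.17 against 1.29) with the right sign. The damage is greatest for the shift and the sustainment test.

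**Conclusion.** Wrong as written. No listed parameter is the post-implementation shift for which power is claimed, and the two conditions set for the first slope cannot both hold for one line. Under the protocol's own planning pattern the shift contrast has the wrong sign and the false deterioration (d about -0.54) exceeds the 0.48 detection limit. Across the three shapes examined the deterioration bias runs from -0.96 to +0.42.

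These sizes rest on 91 equally spaced weekly points, a knot at 12 months after randomisation and the pilot effect sizes, with no variance assumption. The rejection rates do depend on variances the document does not give, so no single rate should be quoted as this trial's error rate. The inconsistency in the text is certain; which model the analysts would in fact fit cannot be known from the article.

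**What to change.** Specify level 1 with four time terms:

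- a lead-in slope;
- a post-randomisation indicator (0 in months 1 to 3, 1 from month 4);
- time since randomisation (0 in the lead-in);
- time since the end of the active phase (0 before it), with one knot at 12 months after randomisation in place of the references to the last year and the second year.

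Then name the tested parameters: arm × post-randomisation indicator is the mean shift, arm × time since randomisation is the slope difference, and arm × time since the end of the active phase is deterioration. Describe any arm difference in the intercept as baseline imbalance, not as an effect. Rerun the Monte Carlo power on this model and restate the figures for shift, slope and deterioration.

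The cost is wording, one simulation rerun, one or two more fixed effects and slightly less precision, with no new sites or data. The plan should also say whether the lead-in slope is common to both arms. In the simulations above, where each site had its own lead-in slope, power for 1.29 per week ranged from 57% to 89% under the assumed variances, so the stated power of at least 80% for slopes should not simply be carried over.
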